##### Attrition

We will compare attrition rates between the two treatment groups and compare demographics and baseline values of FDI and other measures of dropouts to non-dropouts. If dropouts are random, then the results are unbiased. If dropouts are not at random, we will comment on the direction and magnitude of potential biases.

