### Intervention

Each mentored participant will be assigned to a peer mentor. Each mentor will work with no more than three subjects at one time; once all mentors have been assigned one to three subjects, recruitment will stop until the intervention cycle concludes. Cycles may be staggered depending on recruitment and mentor availability.

Each cycle will consist of 10 sessions of 30-60 minute phone calls conducted over a period of eight weeks. The mentor and mentored participant(s) will have two sessions per week for the first two weeks, and one session per week for the remaining six weeks. Current literature supports the use of an expanding-interval schedule of interventions (compared to a massed (single session) or uniform-interval schedule) with evidence that the expanding schedule may help to attenuate long-term recurrence of negative emotions [37]. Phone calls will take place on a secured, monitored conference call line so that no participants will exchange personal contact information. The time of all phone meetings will be scheduled by the research staff, based on availability of mentor and mentored participant(s) and will remain at a fixed time each week. Mentoring sessions will occur only during the scheduled times and mentored participant-mentor contact outside of the mentoring sessions will be specifically prohibited. During each session, participants will also be viewing a slide presentation at the time of the conference call, so that didactic information can be presented. This presentation has been developed by doctoral-level research staff. As previously mentioned, to ensure safety of all participants, a member of the research team will be monitoring all telephone calls. This individual will facilitate the discussion, only if necessary, as well as intervene in any potential safety concerns (e.g., discussion of suicidal ideation) or inappropriate behavior (e.g., bullying).

In an effort to increase adherence, mentored participants will be informed that if they miss two consecutive mentoring sessions, or miss three sessions total over the course of the intervention for non-emergency reasons, they will be removed from the study. Additionally, peer mentors who miss two mentoring sessions (for non-emergency reasons) will be removed from further participation as a mentor. Mentored participants will then be reassigned to a new mentor for the remaining sessions.

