##### Primary Analyses

The primary outcomes are adherence (percent of sessions attended, percent of home exercises completed). The primary analysis method is repeated measure analysis of variance (ANOVA) between the two groups or the non parametric equivalent (Friedman procedure). We will subtract baseline value from the 2- and 4-month assessment values and use residualized change scores from baseline as the outcome. We will use the Tukey-Fisher criteria for post hoc mean/median comparisons under the ANOVA or Friedman model. The same methods will be used for the analyses on NRS and FDI scores.

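### The attrition checks cannot show that dropout is random, so they should not decide whether the results are called unbiased

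*Protocol article*

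**What the plan says.** The Attrition section of the protocol article sets out two checks. Attrition rates are compared between the arms, and the investigators will "compare demographics and baseline values of FDI and other measures of dropouts to non-dropouts". Two outcomes follow. In one, "If dropouts are random, then the results are unbiased". In the other, "If dropouts are not at random, we will comment on the direction and magnitude of potential biases". Neither is tied to a change of analysis.

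Under Primary Analyses, "The primary analysis method is repeated measure analysis of variance (ANOVA) between the two groups", with the Friedman procedure as the nonparametric alternative. On the outcome it says: "We will subtract baseline value from the 2- and 4-month assessment values and use residualized change scores from baseline as the outcome". The same methods are applied to the NRS and FDI.

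Under Intervention, mentored participants are told that if they miss two mentoring sessions in a row, "or miss three sessions total over the course of the intervention for non-emergency reasons, they will be removed from the study". Controls have no mentoring sessions and no corresponding rule.

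**The concern.** In the order in which the section is written, the comparisons decide between two statements: the results are unbiased, or there may be bias to comment on. There are three difficulties.

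- **The checks look at the wrong information.** Dropout that depends on how the adolescent fares during weeks 1 to 8 need not show in baseline values, whatever the sample size.
- **The checks are weak at the planned size.** A null comparison is likely even when dropouts and completers differ.
- **Loss is arm-specific by design.** Removal for missed sessions can happen only in the mentored arm. Classical repeated measures ANOVA and Friedman need both follow-up values, so removed participants without follow-up would leave the comparison, and the remaining mentored group is selected on attendance.

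At stake is a pilot estimate declared free of bias on evidence that cannot support it. The Discussion says a larger controlled trial is to follow.

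**Working it through.** The Attrition section gives no figure to reproduce. Inputs from the protocol article: 29 per group (Sample Size Determination and Power Analysis), so 58 in total; a minimum of 50 (same section); 32 to 48 mentored participants with as many controls (end of the Sample size section), so 64 to 96. It gives no expected dropout rate, so all loss rates below are assumptions. The 29 per group is used only as the planned size.

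**Step 1. Power of the baseline comparison.** Two-sample t-test, two-sided 5%, true difference 0.5 SD. Noncentrality = 0.5 × √(n₁n₂/(n₁+n₂)), with 56 degrees of freedom and critical value 2.003.

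| Dropouts / completers | n₁n₂/(n₁+n₂) | Noncentrality | Power |
|---|---|---|---|
| 6 / 52 | 312/58 = 5.38 | 1.16 | 20.7% |
| 9 / 49 | 441/58 = 7.60 | 1.38 | 27.3% |
| 12 / 46 | 552/58 = 9.52 | 1.54 | 32.9% |

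For 10% to 30% dropout, power is 18% to 36% with 50 randomised and 32% to 61% with 96. With 58 randomised, the difference detectable with 80% power is 1.23 SD for 6 dropouts and 0.92 SD for 12.

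**Step 2. Power of the between-arm comparison.** Fisher's exact test.

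| True loss | 29 per arm | 48 per arm |
|---|---|---|
| 10% vs 20% | 9% | 18% |
| 10% vs 30% | 35% | 61% |

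**Step 3. Both checks together, with loss depending on progress.** Simulation with no true effect and 29 per arm. Mentored-arm loss is 29% and rises with week-4 FDI (logit slope 1.0); control loss is 10% at random; correlations are 0.55 to 0.75. The analysis is baseline-adjusted and complete-case.

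- The baseline check flags 16% to 19% of trials across repeated runs, the arm comparison about 33%, and at least one of them about 43%. About 57% of trials pass both.
- Complete-case bias is about −0.09 SD (−0.08 to −0.09 across runs), an apparent benefit of mentoring. In trials that pass both checks it is no smaller (−0.08 SD). Type I error is about 7%.
- With the slope reversed, so that those doing well leave, the bias is +0.09 to +0.10 SD.

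**Step 4. Loss depending on the later outcome itself.** 29 per arm; in the mentored arm, loss depends on the later outcome and not on baseline.

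| Loss, mentored / control | Pass both checks | Bias | Bias if both passed | Type I error |
|---|---|---|---|---|
| 20% / 10% | 87% | −0.14 SD | −0.13 SD | 11% |
| 30% / 10% | 62% | −0.20 SD | −0.18 SD | 15% |
| 20% / 20% | 93% | −0.14 SD | −0.14 SD | 10% |

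The negative sign follows from the assumed direction of loss. With truly random loss, bias is about 0 and type I error 4% to 5%.

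**Step 5. What a likelihood-based model gains.** In the Step 3 setting it has bias near 0 (−0.001 SD) and standard error 0.236, against 0.242 for complete cases. That result is built in, because dropout there depends on a value that the model uses. When loss depends on the 2-month outcome, the likelihood estimate is still biased by −0.09 SD, against −0.14 SD for complete cases.

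**The case against.** - **The sentence is literally true.** If dropout is completely random, completer results are unbiased, and the section states no significance criterion for randomness. That stands. The fault is drawing the conclusion from these comparisons, which the order of the section implies.
- **The arm comparison is part of the plan and helps.** It is aimed at unequal loss: at 48 per arm, about 67% of trials in the Step 3 scenario are flagged by one check or the other. This stands too, but a third of trials still pass, and when loss rates are equal the arm comparison is uninformative.
- **Case deletion is not stated.** It is a property of the named methods in standard form, and Preliminary Analyses says missing data will be examined. An analysis plan that is not shown may name a missing-data method, so its absence here is not the criticism. The criticism is of the rule and conclusion that the protocol does state.
- **The bias need not favour mentoring.** A reader might infer that it must, because the remaining mentored participants are good attenders. The documents do not support this: nothing links missed calls to worse FDI or NRS, an adolescent who improves may also stop calling, and reversing the assumed slope reverses the bias. No calculation was made for adherence or NRS.
- **The study is an exploratory pilot.** It concedes possible low power and undertakes to evaluate control-group attrition. This limits the severity but does not rescue the inference.

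**Conclusion.** The concern holds in a limited form. Comparing attrition rates and baseline values cannot show that dropout is random, at this sample size or any other, and should not license the word unbiased. The removal rule for missed sessions makes arm-specific loss likely, and the only written response to non-random dropout is commentary.

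The size is moderate: about 0.09 SD in either direction in the week-4 scenario, against a planning effect of 0.52, with type I error near 7%. It is larger, 0.14 to 0.20 SD with type I error of 10% to 15%, if loss depends on the later outcome itself. These figures rest on assumed loss rates, correlations and mechanisms. They also assume that removed participants contribute no follow-up, as removal from the study suggests. The power figures in Step 1 depend only on the number of dropouts and the 0.5 SD difference. The direction of any bias is not established. This should be changed, but it does not undermine the trial.

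**What to change.** 1. Delete the Attrition sentence that declares the results unbiased. Keep the comparisons by arm and by dropout status as description only.
2. Analyse FDI and NRS with a likelihood-based mixed model of all randomised participants with any post-baseline value. Use fixed effects for arm, time, arm-by-time and baseline, and include the weekly values from weeks 1 to 8 that Table 1 already schedules.
3. Because that model removes bias only when dropout depends on observed values, add one sensitivity analysis that shifts the unobserved values by stated amounts until the conclusion changes. Given the uncertain direction, apply shifts both ways.
4. Apply the same sensitivity analysis to adherence, using the weekly treatment-tracking data. As described under Primary Outcomes, the form records visits and missed appointments, so it serves the attendance component.

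The cost is a change of wording and modest extra programming and reporting. FDI, NRS and attendance need no new data collection.

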##### Interview Analysis

The major goal of the interview analysis is to elicit the mentor's and mentored participant's perceptions of the intervention and specific ways in which they found it helpful (or not helpful). Approximately 60 minutes will be recorded with each mentor and selected subject, for a total of 18 interview hours. The interviewer will use a semi-structured script suggests topic areas and questions, but allows adolescents to develop each topic in their own words. All interviews will be transcribed and coded using N*6 software and applying the principles of grounded theory [47,48].

The coders will code each interview for the number and strength of the each of the following types of statements: 1) statements of functioning limitations *or *of functioning abilities; 2) statements of self-efficacy to achieve goals *or *of lack of self-efficacy; 3) statements that mentorship was helpful *or *that it gave little help; 4) statements that learning a pain self-management skill was helpful *or *of little help. The *strength *of a statement will be indicated by the presence of modifiers and will be valued using a table of standard statements. Examples of statements in order of increasing strength: "Mom says I should be able to walk a mile now," "I think I can walk a mile now." "I know I could walk a mile now," "I walked a mile yesterday," "I often walk a mile now." Values of statements regarding functioning and self-efficacy will be compared with changes on quantitative measures for each child to see if the different types of data corroborate each other; and also compared with the values of the child's statements regarding helpfulness of the interventions. Statements regarding the helpfulness of the peer mentorship intervention and skills building therapies will be evaluated for strength and used in the evaluation of the program.

Additional context-based codes may be assigned, using the constant comparison method [49], to identify statements regarding treatment expectations and beliefs, pain expectations and beliefs, fears and anxieties. Coders will carry out this second-level coding to identify specific factors promoting changes in the child's functionality from intake through the mentorship intervention. All statements then will be analyzed to determine if the children's accounts support the Jensen model [12] of behavior change described above.

## Discussion

This is an exploratory pilot study in which good evidence of outcome intervention will depend on the success of a mentor training program which is still in development. We have tried to plan all aspects of recruitment and training carefully, but mentor retention and mentor adherence to a structured intervention protocol may vary with factors we have not considered. We will be evaluating carefully the scheduling, format, and content of communications, as well as the attrition rate for the control group at both assessment timepoints. We considered using electronic communication because of its greater flexibility, but phone communication was selected because it will promote social interaction for those patients who may have stopped attending school and other activities outside the home. Peer group therapy is another alternative to introduce peer modeling and reinforcement into a treatment program to improve functioning; but our experience suggests that group meetings often prove impractical for adolescents and families with busy daily schedules. Sample size has been estimated based on other studies of pediatric pain that have evaluated CBT-based interventions and reported a large effect size. We may not have the same effect size and may have underpowered this pilot study. Finally, some patients' participation in recommended therapies may be limited by factors, such as insurance authorizations, over which we have no control.

This exploratory pilot study will enable us to refine the features of the peer-mentorship model - mentor training, structure and content of the manual and protocol, length and format of interactions - and to test our hypotheses that mentors and mentored participants will find this intervention acceptable and that mentored participants will demonstrate improved functioning in comparison to a usual care control group by follow-up. These findings will be disseminated in papers submitted to peer-reviewed journals. We then plan to test the refined model in a controlled R01 trial with a larger sample and longer-term subject follow-up, with a mediator/moderator model.

## List of Abbreviations Used

ANOVA: Analysis of variance; BDI-II: Beck Depression Inventory: 2nd edition; CASI: Child Anxiety Sensitivity Index; CBT: Cognitive-behavioral therapy; CAM: Complementary and alternative medicine; FDI: Functional Disability Inventory; NRS: Numerical Rating Scales; PI: Principal investigator; RAP: Recurrent abdominal pain; RCADS: Revised Child Anxiety and Depression Scale.
